### Analysis

All primary analyses will be by intention-to-treat. The primary outcome (monthly number of CNS-active medications over 6 months pre- and post-intervention) will be analysed using a general linear mixed effects regression model; time will be specified as a continuous variable and a common secular trend will be imposed across all study arms with the effect of the intervention modelled as a slope deviation from the secular trend. The analysis will adjust for the size of each home as a fixed effect. Random intercepts and slopes for time will be specified for the unit of randomization (group of homes) and for the individual resident to account for cluster and individual autocorrelation. The primary comparison between the arms’ 6-month post-intervention will be estimated using least square mean differences, together with 95% confidence intervals. Because the traditional two-stage testing approach (i.e. an interaction test followed by dropping the interaction term if non-significant) can lead to bias in factorial trials [30], we will present both four-arm and factorial analyses.

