### Power

In head-to-head trials where small changes to existing initiatives are tested and where each sequential change in the process of optimization is expected to offer cumulative benefit, it is necessary to power for small changes. In this pragmatic trial, the sample size is dependent on the number of providers who sign up for the reports. At the time of study launch, there will be physicians working in over 200 nursing homes who have signed up to receive the HQO Practice Reports. After grouping homes sharing providers together, we anticipate having approximately 160 clusters, with an average of 350 beds per cluster. In a 2 × 2 factorial design assuming no interaction and similar effects for each intervention, a test of each intervention at 6 months in an ANCOVA design will achieve 90% power to detect an absolute mean difference of 0.3 in the primary outcome (i.e. a reduction across arms in the mean number of CNS-active medications from 3 to 2.7). Based on previous data, we have assumed a standard deviation of 4, an intracluster correlation coefficient of 0.05, a cluster autocorrelation of 0.8, and an individual autocorrelation of 0.9 [31]. In the presence of an interaction effect, switching to a 4-arm comparison would require a slightly larger difference of 0.4 in the mean number of medications.

For our secondary outcome (any monthly prescription of antipsychotics), our sample size will achieve 90% power to detect an absolute difference of 1.2% (or a relative difference of 6%) from a reference arm proportion of 20% using six monthly pre- and post-intervention measurements, with an intracluster correlation coefficient of 0.05, a cluster autocorrelation of 0.8, and an individual autocorrelation of 0.9. In the presence of an interaction effect, switching to a 4-arm comparison would require a larger relative difference of 8.5%.

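### The cluster random slope in the primary model is not tied to the intervention term; read literally, under the plan's own variance assumptions, the primary confidence intervals would be far too narrow.

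*Protocol article*

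**What the plan says.** The Analysis section of the protocol article takes as primary outcome the "monthly number of CNS-active medications over 6 months pre- and post-intervention". Time is continuous, one secular trend is common to all arms, and "the effect of the intervention modelled as a slope deviation from the secular trend". On correlation it says: "Random intercepts and slopes for time will be specified for the unit of randomization (group of homes) and for the individual resident", and gives the purpose as "to account for cluster and individual autocorrelation". The comparison at six months after the intervention "will be estimated using least square mean differences, together with 95% confidence intervals". No cluster-by-month term, random slope specific to the post-intervention period, or choice of variance estimator is named.

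The Power section, for the same outcome, assumes a standard deviation of 4 and "an intracluster correlation coefficient of 0.05, a cluster autocorrelation of 0.8, and an individual autocorrelation of 0.9", with about 160 clusters averaging 350 beds. It uses the same three correlations for monthly antipsychotic prescribing with six measurements before and six after.

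The later paragraphs on secondary outcomes carry the primary model over to monthly mean dose and, in logistic form, to the monthly binary outcomes.

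**The concern.** A cluster autocorrelation of 0.8 means that a fifth of the between-cluster variance changes from period to period and is shared by every resident of the cluster. Averaging over 350 residents does not reduce it. The analysis model gives each cluster an intercept and one straight line in time. An effect that begins at the intervention is a bend at the middle of the series, and a straight line cannot absorb a cluster's own bend. If the random slope runs over all 12 months while the effect starts at month 6, the model judges the bend mainly against resident-level noise divided by cluster size. The shared month-to-month variation that dominates the power calculation is then left out of the standard error. At stake is the coverage of the primary confidence intervals, and of those for the monthly outcomes that reuse the structure.

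**Working it through.** **Inputs (Power section).** SD 4, ICC 0.05, cluster autocorrelation (CAC) 0.8, individual autocorrelation (IAC) 0.9, 160 clusters (80 per factor level, 40 per arm), m = 350. Assumed, because the section states no alpha for the trial: two-sided 0.05.

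**Step 1: reproduce the plan's figures.**
- Design effect = 1 + 349 × 0.05 = 18.45.
- Correlation of cluster means r = (m·ICC·CAC + (1 − ICC)·IAC) / 18.45 = (14 + 0.855) / 18.45 = 0.805.
- ANCOVA variance = 2 × 16 × 18.45 × (1 − 0.805²) / (350 × 80), so SE = 0.086. Detectable difference = (1.960 + 1.282) × 0.086 = 0.279, stated as 0.3. With 40 clusters per arm it is 0.395, stated as 0.4.
- Antipsychotics, 6 + 6 months: replace SD² by 0.20 × 0.80 = 0.16 and (1 − r²) by A − r²/A, with A = (1 + 5r)/6 = 0.838. The detectable difference is 1.19% (stated 1.2%), and 1.68% for four arms, or 8.4% relative (stated 8.5%).
- With CAC = 1 the factorial figures would be 0.048 and 0.19%. The stated figures therefore rest on period-specific cluster variation.

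**Step 2: variance components implied by those inputs.** Cluster variance 16 × 0.05 = 0.80, split into 0.64 persistent and 0.16 by month. Resident variance 15.2, split into 13.68 persistent and 1.52 residual. The monthly mean of a cluster of 350 carries 0.16 of shared monthly variance against 1.52/350 = 0.0043 of averaged residual variance.

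**Step 3: fit the stated model to that structure.** Let h be months since the intervention (0 before, 1 to 6 after), S the true covariance of a cluster's 12 monthly means, and V the covariance the fitted model converges to. For 80 versus 80 clusters and a difference of six slope units:
- model SE = 6 × √[(4/160) / (h′V⁻¹h)]
- true SE = 6 × √[(4/160) × h′V⁻¹SV⁻¹h / (h′V⁻¹h)²]
- type I error = 2 × [1 − Φ(1.96 × model SE / true SE)]

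| Reading of the model | m | Model SE | True SE | Ratio | Type I error |
|---|---|---|---|---|---|
| Cluster slope on 12-month time, effect from the intervention | 350 | 0.020 | 0.112 | 5.5 | 72% |
| Same | 200 | 0.026 | 0.104 | 4.0 | 63% |
| Same | 100 | 0.034 | 0.091 | 2.7 | 47% |
| Same | 50 | 0.042 | 0.078 | 1.9 | 29% |
| Cluster slope on post-intervention time | 350 | 0.052 | 0.052 | 1.00 | 5% |
| Effect and cluster slope on one 12-month time variable | 350 | equal to true | – | 1.00 | 5% |
| 12-month slope plus cluster-by-month effect | 350 | 0.052 | 0.052 | 1.00 | 5% |

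Simulation at m = 350 agrees: ratio 5.7 and 72% for the first row, 4.3% for the slope on post-intervention time (400 runs each), and 5.5% with the cluster-by-month effect (200 runs).

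**Step 4: vary the form of the cluster correlation under the first reading (m = 350).** If correlation decays to 0.8 at 6 or at 12 months, the ratio is 6.9 or 4.9 and type I error 78% or 69%. If the cluster drift is linear, the ratio is 1.00 and the error 5%.

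**The case against.** A reader might infer that, because the model has no cluster-by-month effect, its primary intervals must be invalid. The documents do not support that. The model does contain a cluster-by-time term, the random slope, and its stated purpose is to deal with autocorrelation. The article does not say whether that slope is on calendar time or on the term carrying the effect. In the second case the error rate is 5% with no cluster-by-month term, even when the truth contains one. This part of the objection stands and makes the conclusion conditional.

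Three further points have weight:
- **Planning inputs do not fix an analysis model.** The primary power figure is an ANCOVA calculation in which 0.8 is a single correlation, so it does not settle the month-to-month pattern. Constant correlation at all lags is shown only by the antipsychotic figure and is carried over to the primary outcome by inference. Step 4 shows that decaying correlation gives the same problem and linear drift removes it.
- **350 counts beds.** Only residents whose responsible physician signed up are analysed, in an open cohort. The calculation uses equal, complete, closed clusters. Smaller clusters shrink the problem without removing it.
- **Coding of random effects and choice of variance estimator are often left to the analysis plan.** Silence on robust standard errors is no fault in itself. The point here is that the article does state its random effects, and on their literal reading they do not match the cluster structure of its own Power section.

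The valid readings do not settle the matter by themselves. A slope on post-intervention time is not stated. One time variable for both effect and slope would have the arms diverging during the pre-intervention months.

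**Conclusion.** The point holds conditionally. As written, the primary analysis admits one reading with about 72% type I error and others with 5%, under identical planning values. The literal one, with the cluster slope on 12-month time and the effect starting at the intervention, understates the standard error by a factor of about 5.5 at 350 residents per cluster, 2.7 at 100 and 1.9 at 50. This rests on the plan's SD, ICC and autocorrelations, two-sided alpha of 0.05, balanced closed clusters, model-based standard errors, and cluster variation over time that is not linear. The monthly dose and binary outcomes inherit the specification, but the size for the binary (logistic) outcomes was not computed. The ambiguity should be removed before the outcome analysis, since the validity of the primary interval depends on it.

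**What to change.** In the primary model, and in the monthly outcomes analysed like it, specify one of the following:
- a cluster-level random slope on the post-intervention time term that carries the intervention effect; or
- a cluster-by-month random effect in addition to the stated terms.

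Either is enough under the plan's variance structure; both are not required. Cluster-robust standard errors at the unit of randomisation, with a small-sample correction, are an alternative or an added safeguard.

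The cost is a sentence of wording and some code. Intervals become wider than the literal model would report: SE about 0.052 instead of 0.020, roughly 2.5 times. The detectable difference at 90% power is then 3.24 × 0.0519 = 0.17 for the factorial comparison and 3.24 × 0.0734 = 0.24 for four arms, both inside the planned 0.3 and 0.4.

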### Experimental conditions

All participants will be sent a version of the HQO Practice Reports (Additional file 3) which include the BCTs outlined above. For the study, we manipulated two features of the feedback which may be thought of as experimental factors: (1) the comparator (average vs top quartile) and (2) the framing of the feedback content (patients at risk vs patients safe from risk). Thus, we created four versions of the HQO Practice Reports (Table 2).

**Table 2 Tab2:** Factorial 2 × 2 diagram of trial arms

	Factor 1: Comparator [Top quartile/average]	
Factor 2: framing [Benefit framing/risk framing]	75th percentile/benefit framing	Average/benefit framing
	25th percentile/risk framing	Average/risk framing

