### Factor 1: benchmark/comparator in feedback reports

Participants’ prescribing rates will be compared to either the provincial average or top performing peers (top quartile). Prior to this trial, HQO practice profiles compared performance of the recipient to provincial averages on a summary page and both provincial and regional averages on the detailed indicator pages. One of the recently published suggestions for practice feedback design is to use ‘a single comparator that effectively communicates the key message’ [2]. Comparing recipients to the top 10% of their peers is more likely to achieve this aim than comparing to the average score of all their peers [4]. However, HQO felt that a benchmark of the top 10% may risk unintended discontinuation of medications that may be actually be appropriate, rather than a careful review of medication use. The top quartile was decided to be acceptable for the purposes of the trial while maintaining the essential needs of the HQO program that avoids unnecessary harms to residents in LTC.

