### Factor 2: framing of performance in feedback reports

Factor 2 tests the framing of the feedback reports to be either ‘risk-framed’ (e.g. emphasizing patients at risk of harms) or ‘benefit-framed’ (e.g. emphasizing patients *safe* from risk of harms) without changing the underlying data. Decision-making is affected by the way a problem (or in this case, feedback) is framed [11, 23]. Framing has been shown to affect clinical decision-making of physicians in prior studies [24], with the perceived level of risk involved in the decision posited as a mediating factor [25]. Prospect theory describes how people may differentially weigh the potential gains and potential losses, emphasizing the importance of risk aversion in decision-making [26].

We operationalized *risk framing* by providing feedback on the proportion of patients receiving high-risk medications and describing this as patients *at risk of harm* from those medications. This framing was designed to be presented in two ways: visually using the line graph with percentage of patients at risk on the *y*-axis and red colour emphasis in the graph and in text form with the statement ‘Nn additional/fewer resident(s) in my practice may be/are at increased risk associated with benzodiazepines’ (see Additional file 4). We operationalized *benefit framing* by providing feedback on the (1-X)% of patients in whom high-risk medications were avoided and described this as patients *safe from the risks of harm* associated with those medications. This framing was designed to be presented in two ways: using a line graph with percentage of patients safe from risk on the *y*-axis and green colour emphasis in the graph and in text form with the summary statement ‘No additional/fewer resident(s) in my practice may be/are safe from risks associated with benzodiazepines’ (see Additional file 4).

We refined the language for risk framing and the associated colour changes iteratively through a user-testing process (Additional file 1) to ensure that the emotional responses invoked would encourage action rather than distract from the task of improvement [6].

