### Allocation

Cluster randomization is necessary because the intervention is delivered to physicians who may work collaboratively with other health care professionals. To prevent contamination that could occur when physicians work in multiple nursing homes, we have grouped homes that share physicians into clusters. Thus, the unit of randomization will be groups of one or more nursing homes sharing physicians. An independent statistician will randomize these clusters independently by the two factors (resulting in four experimental conditions), stratifying by total number of beds in the cluster [27], using a randomly permuted block design of length four. Physicians who sign up for the report after randomization and who belong to a cluster already assigned will be provided the same allocation as others in their group to avoid contamination.

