We will examine whether the language in the key message in the report (i.e. the bolded statement declaring the number of additional/fewer patients are at risk from (or safe from risks of) benzodiazepines) is differentially associated with changes in prescribing. This is an uncontrolled element of the intervention, dependent on the observed distribution of performance of physicians relative to their peers. The relative performance of the physician compared to the comparator may act as an effect modifier because having additional patients at risk of harm or fewer patients safe from harm may invoke different responses than having fewer patients at risk or more patients safe. Additionally, it is plausible that recipients may respond more actively to simpler language (e.g. ‘7 additional residents in my practice may be at increased risk of harm’ may be easier to interpret than ‘7 fewer residents in my practice are safe from risk of harm’) because the simpler wording may make it easier for recipients to evaluate their performance relative to the comparator and respond accordingly. Thus, we will adjust for relative performance (i.e. better, same, or worse than comparator) and clarity of the statement (i.e. additional versus fewer) as a covariate and then conduct planned subgroup analyses to examine differential effects of the intervention across these subgroups (while acknowledging unmeasured confounding and uncertain power in these subgroup analyses).

We will also explore potential effect modification by baseline prescription rate, ownership status of nursing home, beds in the home, location (urban/rural), specialist utilization (proportion of patients with geriatrician or psychiatrist consultation within 6 months), plus primary physician characteristics (sex, years’ experience), as well as patient characteristics (age, sex, time at facility, levels of function and cognition). A planned sensitivity analysis will examine effects by extent of exposure to the intervention (i.e. fidelity of receipt, which assesses whether physicians downloaded their report).

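### Relative performance and message wording are partly set by the assigned arm, so comparator contrasts within performance strata, and both factors' contrasts within wording subgroups, are not randomised comparisons

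*Protocol article*

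**What the plan says.** The protocol article randomises two features of the report, comparator and framing; under Allocation, a statistician "will randomize these clusters independently by the two factors". The framing is altered "without changing the underlying data". In the risk-framed report the key message is a count followed by "additional/fewer resident(s) in my practice may be/are at increased risk associated with benzodiazepines"; in the benefit-framed report it counts residents who are safe from those risks.

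The Analysis section then asks whether the language of that message goes with different changes in prescribing. It treats the message as uncontrolled and dependent on where a physician stands among peers. It plans as follows: "we will adjust for relative performance (i.e. better, same, or worse than comparator) and clarity of the statement (i.e. additional versus fewer) as a covariate". After that it will "conduct planned subgroup analyses to examine differential effects of the intervention across these subgroups", with a caveat about unmeasured confounding and uncertain power. It does not say that the assigned arm helps determine both variables, which of the quarterly reports defines them, or which model the adjustment belongs to.

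**The concern.** The comparator against which a physician is better, same or worse is the one the cluster was randomised to. A physician whose rate lies between the two thresholds changes class with the allocation. Showing a discrepancy to more recipients is also the stated reason, in the Abstract and Background, for using a higher benchmark. Holding relative performance fixed therefore blocks at least part of the route by which Factor 1 is supposed to act, and sets different kinds of physician against each other.

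The words *additional* and *fewer* carry no information beyond framing and relative performance. Comparing framings inside one wording group means comparing physicians on opposite sides of their comparator.

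These analyses are meant to explain how comparator and wording work. As specified, they could hide a comparator effect or produce a framing effect that is not there.

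**Working it through.** **Inputs.** From the protocol article: the two comparators and two framings (Experimental conditions, Factor 1, Factor 2), independent cluster randomisation (Allocation), and the definitions of the two variables (Analysis). The plan gives no figure on this point to reproduce. *Assumed, not in the document:* physician baseline prescribing Z is standard normal, lower is better, with no ties; the average sits at 0 and the top-quartile benchmark at −0.674; the baseline-to-follow-up correlation R is 0.6, 0.8 or 0.9.

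**Step 1: wording (no assumption needed).**

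| Standing against assigned comparator | Risk-framed | Benefit-framed |
|---|---|---|
| Worse | additional at risk | fewer safe |
| Better | fewer at risk | additional safe |

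Each performance-by-wording cell holds one framing only, so no framing contrast exists inside it. Within *additional*, risk-framed physicians are all worse than their comparator and benefit-framed physicians all better.

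**Step 2: who falls in each stratum.** Share classed worse: 1 − Φ(0) = 50% under the average, and 1 − Φ(−0.674) = 75% under the top quartile. The 25% in between change class with the arm.

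Mean baseline is φ(c)/(1 − Φ(c)) above a cut c and −φ(c)/Φ(c) below it:
- Worse: 0.798 (average) and 0.424 (top quartile), gap −0.37 SD.
- Better: −0.798 and −1.271, gap −0.47 SD.
- *Additional*, risk minus benefit: 0.798 + 0.798 = 1.60 SD under the average; 0.424 + 1.271 = 1.70 SD under the top quartile; 0.573 + 0.956 = 1.53 SD pooled over comparators. The sign reverses within *fewer*.

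The −0.37 and −0.47 gaps also arise between comparators within a wording subgroup once framing is in the model, as it is in both the factorial and the four-arm analysis.

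**Step 3: if the message works.** Suppose being told *worse* lowers prescribing by d and nothing else matters.
- The comparator effect is 0.75d − 0.50d = 0.25d overall, but 0 within *worse* and 0 within *better*.
- The framing effect is truly 0. Within *additional*, the risk-framed have fallen by d and the benefit-framed by nothing, a difference of d; within *fewer* the difference is d in the opposite direction.

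Suppose instead that the fall is b per SD of displayed shortfall. The mean shortfall among the worse is 0.798 (average) or 0.424 + 0.674 = 1.098 (top quartile). The overall comparator effect is 0.75 × 1.098b − 0.50 × 0.798b = 0.42b. Within *worse* it is 1.098b − 0.798b = 0.30b, and within *better* 0. Part of the effect is lost, not all.

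**Step 4: if neither factor nor message does anything.** A baseline gap g becomes R × g on follow-up level and (R − 1) × g on change.
- Comparator, adjusted for relative performance: the stratum weights are 0.625 × 0.6 × 0.4 = 0.150 (worse) and 0.375 × 1/3 × 2/3 = 0.083 (better), so g = (−0.374 × 0.150 − 0.473 × 0.083)/0.233 = −0.41. For R = 0.6, 0.8, 0.9 this gives −0.25, −0.33, −0.37 SD on level and +0.16, +0.08, +0.04 SD on change.
- Framing within *additional*: +0.98 to +1.47 SD on level and −0.65 to −0.16 SD on change, reversed within *fewer*.
- Framing within *worse* or *better*, and framing adjusted for performance and wording together: 0.00.

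A simulation of 2,000,000 physicians with no effect of either factor gives these values. Neither scale is the plan's mixed model, so they show direction and mechanism rather than the bias that model would report.

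**The case against.** The strongest reply is that the trial's questions are answered elsewhere. The primary analysis is by intention-to-treat, factorial and four-arm, and its only stated covariate is home size. The message-language analysis is a separate, associational aim with a stated caveat. That stands: a reader might infer that the main comparisons are compromised, but nothing in the document puts these two variables into the primary model.

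Three further limits stand:
- **Framing.** It would be wrong to reject every framing result. If relative performance is taken from the first report, it depends on baseline and comparator only, and framing is randomised independently of both. Framing effects within performance strata are then valid. If later reports count, this defence fails.
- **Size.** A reader might multiply the gaps by a cluster SD of √(0.05 × 16) = 0.89 medications and set the result against the target of 0.3. The document does not support that. The key message concerns physicians' benzodiazepine prescribing, whereas that SD is for the CNS-active count at cluster level; and gaps in baseline level are not bias in an estimate built on slope deviation.
- **Existing plans.** Effect modification by baseline prescription rate is already planned. In the simulation, adding an exactly measured baseline level to the adjusted model returned the null comparator effect to 0.00. But the plan lists this modifier separately and does not say it enters these models.

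The caveat does not settle the matter. It speaks of unmeasured confounding; this dependence is known and built in by the design.

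**Conclusion.** The point holds for a defined set of planned, non-primary analyses: the comparator effect adjusted for or stratified by relative performance, and both factors' effects within wording subgroups. These are not randomised comparisons, and the single-framing cells in Step 1 follow from the report design without any assumption. The percentages and SD gaps rest on the normal model, and the null results also on R. A comparator effect of exactly zero within strata needs a purely binary response to the message; under a graded response only part is lost. The primary analyses as written are not affected, and framing within performance strata is sound if the first report defines performance. This should be fixed, but it does not threaten the main result.

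**What to change.** 1. State that relative performance to the assigned comparator, and wording, do not enter the primary model.
2. Classify every physician, in all four arms, by pre-launch performance against both thresholds: better than the top-quartile benchmark, between benchmark and average, or worse than average. Use this arm-independent variable as the covariate and effect modifier. If physicians respond mainly to being told better or worse, the comparator effect should appear chiefly in the middle band, where the message switches.
3. Examine wording as the framing-by-band interaction.
4. Drop assigned-comparator performance and wording as covariates and subgroup definers, or report them only as non-causal description, naming the report from which they are taken.

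The cost is analysis wording only. Both thresholds and the physicians' baseline rates are needed to produce the reports, so no new data are required. The change should be made before any unblinded analysis.
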